### Intervention Protocol

All participants receive conventional comprehensive rehabilitation treatment, including speech and cognitive training, social skill training, occupational therapy, sensory integration training, and music therapy [35,36], for 30 minutes per session once daily, 5 times per week, for 12 weeks in total.

#### rTMS-Only Group

The rTMS intervention is administered using a CCY-1 TMS device (Yiruide Medical Equipment New Technology Co., Ltd) with a circular coil. Before the first treatment session, the resting motor threshold (RMT) is determined by identifying the cortical representation of the contralateral abductor pollicis brevis muscle within the primary motor cortex (M1). The optimal stimulation site is defined as the location that consistently produces the maximum amplitude (>50 μV) and shortest latency motor-evoked potential in the relaxed abductor pollicis brevis muscle. RMT is defined as the minimum stimulation intensity required to induce motor-evoked potentials of ≥50 μV in at least 5 of 10 consecutive trials [37,38].

During treatment sessions, participants are seated and wear a positioning cap. The bilateral DLPFC is targeted sequentially: the left DLPFC during weeks 1 to 6 and the right DLPFC during weeks 7 to 12 [2]. This sequencing is based on the hypothesis of hemispheric excitation-inhibition imbalance in ASD [39]. The frequency is set to 1 Hz, and the stimulation intensity is set to 80% the RMT with 400 pulses each time at a 20-second interval every 10 pulses 5 times a week for a total of 12 weeks as a course of treatment. Each session lasts approximately 20 minutes. Following rTMS, participants listen to unmodulated natural environmental sounds or music through headphones for an additional 20 minutes to match the total treatment duration of the combined intervention.

#### rTMS Combined With AIT Group

In addition to the standard rehabilitation treatment, participants in this group receive a combination of rTMS and AIT. For the first 6 weeks, the left DLPFC is targeted, followed by right DLPFC stimulation in the subsequent 6 weeks. The 2 treatments are administered simultaneously, with each session consisting of 20 minutes of rTMS followed by 20 minutes of AIT for a total session duration of 40 minutes. The rTMS protocol matches the parameters used in the rTMS-only group.

The AIT intervention is delivered using the Elite RT510 AIT instrument (Shenzhen Elite Medical Equipment Co, Ltd), a digital integrated therapy device. Participants wear headphones during the AIT sessions. The operator selects the appropriate audio filtration settings based on the participant’s age (distinguishing between those over and under 4 years of age) and then plays a series of filtered and modulated music CDs according to the established AIT protocol [40]. The treatment process involves precise control of sound intensity (“sound level”) and attenuation values following a fixed playback sequence. All equipment parameters are reset after each session.

#### Sham rTMS Group

Participants in this group receive conventional comprehensive rehabilitation treatment as well as sham rTMS stimulation using a “sham coil” with the same appearance as that of the active TMS coil. The sham stimulation parameters, including sequence, sound, and frequency, match those of the rTMS-only group. Additionally, during the 20 minutes following the sham rTMS, participants listen to unmodulated and unfiltered natural environmental sounds or music, similar to the rTMS-only group.

### Outcome Measures

#### Primary Outcome Measures

##### ABC Measure

This 57-item scale [41] completed by parents is suitable for screening and assisting in the diagnosis of ASD in individuals aged 8 months to 28 years. It evaluates behavioral symptoms across 5 factors: sensory abilities, communication abilities, motor skills, language, and self-care. Each item is scored on a 4-point scale. A total score of ≥53 indicates a screening cutoff for ASD, whereas a total score of ≥67 indicates a positive diagnosis of ASD.

##### Childhood Autism Rating Scale

This 15-item scale [42] is used to assess symptom severity in children with ASD aged ≥2 years. Qualified personnel will conduct the assessments, with each item scored from 1 to 4. A total score of 30 to 36 with fewer than 5 items with a score below 3 indicates mild to moderate ASD; a total score of >36 with at least 5 items with a score above 3 indicates severe ASD.

### Secondary Outcome Measures

#### Strengths and Difficulties Questionnaire

Developed by [name] [43], this 25-item questionnaire is used to assess emotional and behavioral problems in individuals aged 2 to 17 years, including those with ASD. The Strengths and Difficulties Questionnaire (SDQ) evaluates 4 areas of difficulty: emotional symptoms, conduct problems, hyperactivity, and peer relationship problems, as well as prosocial behavior. Parents rate their children’s emotional and behavioral performance over the previous 6 months on a 3-point Likert scale (0=“not true,” 1=“somewhat true,” and 2=“certainly true”). Higher scores on the difficulty scales indicate more severe problems, whereas higher scores on the prosocial scale indicate better prosocial behavior. The Cronbach α coefficient is 0.78, demonstrating good reliability and validity.

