**Methods:**

This is a randomized, sham-controlled trial that will recruit 80 children aged 2 to 6 years with a confirmed ASD diagnosis. The randomization of the first 8 participants in this study used a 1:1:1 ratio. To more effectively test the core hypothesis (ie, the efficacy of the combined intervention), greater statistical power will be concentrated on the intervention group (rTMS+AIT), and the randomization ratio was ultimately adjusted to 2:1:1—specifically, (1) rTMS combined with AIT (n=40), (2) rTMS alone (n=20), or (3) sham rTMS (n=20). Primary outcome measures include the Autism Behavior Checklist and Childhood Autism Rating Scale. Secondary outcomes are the Strengths and Difficulties Questionnaire and Repetitive Behavior Scale–Revised. Assessments will be conducted at baseline, an interim time point, and immediately after the intervention. Data will be analyzed using SPSS (version 25.0; IBM Corp).

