**Figure 1. F1:**
[figure not shown]
Flowchart of the trial. ABC: Autism Behavior Checklist; AIT: auditory integration training; ASD: autism spectrum disorder; CARS: Childhood Autism Rating Scale; RBS-R: Repetitive Behavior Scale–Revised; rTMS: repetitive transcranial magnetic stimulation; SDQ: Strengths and Difficulties Questionnaire.

**Table 1. T1:** Schedule of the participant assessments.

	Study period									
	Baseline (week –1)	Allocation (week 0; T0)	Treatment phase—left DLPFC^a^			Interim time point (T1)	Treatment phase—right DLPFC			Posttreatment time point (week 13; T2)
			Weeks 1-2	Weeks 3-4	Weeks 5-6		Weeks 7-8	Weeks 9-10	Weeks 11-12	
Enrollment										
Eligibility screen	✓									
Informed consent	✓									
Randomization		✓								
Interventions										
rTMS^b^+AIT^c^ group			✓	✓	✓		✓	✓	✓	
rTMS group			✓	✓	✓		✓	✓	✓	
Sham rTMS group			✓	✓	✓		✓	✓	✓	
Assessment										
ABC^d^		✓				✓				✓
CARS^e^		✓				✓				✓
SDQ^f^		✓				✓				✓
RBS-R^g^		✓				✓				✓

a DLPFC: dorsolateral prefrontal cortex.

b rTMS: repetitive transcranial magnetic stimulation.

c AIT: auditory integration training.

d ABC: Autism Behavior Checklist.

e CARS: Childhood Autism Rating Scale.

f SDQ: Strengths and Difficulties Questionnaire.

g RBS-R: Repetitive Behavior Scale–Revised.

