### Statistical Analysis

Statistical analyses will be conducted using SPSS. All participants, including the first 8 randomized under the original scheme, will be analyzed according to the intention-to-treat principle. At baseline, continuous variables among the 3 groups will be compared using the Kruskal-Wallis test, whereas categorical variables will be compared using the chi-square test to assess the balance of demographic and clinical characteristics (including age, gender, and baseline scores on all outcome measures) across the randomized groups.

Data normality will be assessed, and appropriate statistical tests will be selected accordingly. For normally distributed measurement data, between-group comparisons will be conducted using one-way ANOVA, and within-group pretest-posttest treatment comparisons will be made using paired-sample 2-tailed *t* tests presented as means and SDs. For nonnormally distributed data, nonparametric tests will be used, with results reported as medians and IQRs. *P*<.05 will be considered statistically significant.

In addition to the primary end-point comparisons at study completion, an exploratory interim analysis of outcomes at 6 weeks will be performed to preliminarily assess the effects of left DLPFC stimulation.

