## Discussion

We hypothesize that, compared to the sham stimulation control group, participants with ASD receiving the active rTMS combined with AIT intervention will exhibit significant improvements in core symptoms such as social difficulties and stereotyped behaviors as measured using standardized scales such as the ABC, CARS, RBS-R, and SDQ. This study aims to provide the latest evidence-based support for the efficacy of this combined intervention approach.

Although preliminary studies have reported positive effects of rTMS combined with AIT in ASD, most have lacked blinding and placebo controls. By implementing a double-blind, sham-controlled design, this trial will address that key methodological limitation. If the results align with our hypotheses, they will provide the first clear demonstration of the specific therapeutic benefits of this combined intervention, thereby advancing the evidence level in this field from the exploratory stage to preliminary validation.

The core strength of this study lies in its rigorous methodological design. As a prospective randomized controlled trial, it uses a double-blind, sham stimulus–controlled approach, which minimizes the potential for expectation and observer biases during the evaluation process, thereby strengthening the causal inferences that can be drawn from the observed efficacy differences. Additionally, the study uses recognized, standardized assessment tools, including the ABC, CARS, SDQ, and RBS-R, to provide a comprehensive and objective evaluation of the core symptom domains in ASD. This assessment combination ensures good reliability and clinical relevance of the study results. Finally, the rTMS and AIT interventions are noninvasive, well tolerated, and easy to implement in clinical settings. These features support participant compliance and trial feasibility and, if the interventions prove effective, will facilitate wider clinical translation as a safe, scalable treatment option for children with ASD.

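### The SDQ's 6-month reference period reaches back before treatment for about 77% of the 6-week rating and 50–54% of the week-13 rating, which weakens this secondary outcome

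*Protocol article*

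**What the plan says.** The Strengths and Difficulties Questionnaire section has parents rate behaviour "over the previous 6 months on a 3-point Likert scale". Table 1 schedules the SDQ at allocation (T0), at the interim visit (T1) between the two treatment phases, and at the "Posttreatment time point (week 13; T2"). The Statistical Analysis section puts the interim visit at 6 weeks: "an exploratory interim analysis of outcomes at 6 weeks will be performed", with the aim of a first look at left-sided stimulation. The rTMS-Only Group section gives the treatment phases as "the left DLPFC during weeks 1 to 6 and the right DLPFC during weeks 7 to 12". The Abstract lists no visit after the end of treatment: "Assessments will be conducted at baseline, an interim time point, and immediately after the intervention".

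The SDQ is a secondary outcome ("Secondary outcomes are the Strengths and Difficulties Questionnaire and Repetitive Behavior Scale–Revised"). The Discussion nevertheless includes it in the efficacy hypothesis, where improvement is to be judged "as measured using standardized scales such as the ABC, CARS, RBS-R, and SDQ". No section gives a different reference period for T1 or T2, and the limitations in the Discussion do not mention recall.

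**The concern.** A rating that covers 6 months describes 6 months of behaviour. When treatment started only 6 or 13 weeks earlier, much of what the parent is asked to describe happened before the child was treated. The same pre-treatment weeks also lie inside the baseline window, so the baseline and follow-up scores partly describe the same period.

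Both kinds of SDQ comparison in the Statistical Analysis section are affected: the between-group tests and the within-group paired tests. The 6-week analysis suffers most. Separating the two phases is also hard, because the T1 and T2 windows are only 6 to 7 weeks apart and so share 19 to 20 of their 26 weeks.

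At stake is the reading of a null or small SDQ result, which could come from a weak treatment effect, from the recall period, or from both. An analysis plan cannot repair this afterwards, because the period is fixed when the parent completes the form.

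**Working it through.** The article gives no figure for SDQ power or sensitivity, so there is none to reproduce. Its only sample-size calculation is for the ABC, and nothing below depends on it.

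**Inputs from the article**
- Reference period: 6 months, taken as 26 weeks (SDQ section).
- T1: 6 weeks after treatment starts (Statistical Analysis; Table 1).
- T2: week 13, so 12 to 13 weeks after treatment starts (Table 1).
- Arms: "1) rTMS combined with AIT (n=40), (2) rTMS alone (n=20), or (3) sham rTMS (n=20") (Abstract). Dropout of about 20% and two-sided α of .05 (Sample Size).

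**Share of the window before treatment** = 1 − (weeks since treatment start) / 26
- T1: 1 − 6/26 = 0.77
- T2, start of week 13: 1 − 12/26 = 0.54
- T2, end of week 13: 1 − 13/26 = 0.50

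With a baseline rating at week 0, these are also the shares of each follow-up window that overlap the baseline window. Sensitivity to the definitions: if T1 falls at 7 weeks, the share is 1 − 7/26 = 0.73. If 6 months is counted as 24 weeks, the shares are 0.75 at T1 and 0.46 to 0.50 at T2.

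**Attenuation, if parents average evenly over the window**
- Full effect from day 1: observed/true = 6/26 = 0.23 at T1, and 12/26 to 13/26 = 0.46 to 0.50 at T2.
- Effect building linearly over 12 weeks: observed/current = about 0.12 at T1 and 0.23 to 0.27 at T2.

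**Illustrative power** (two-sample t test, combined arm versus one control arm)
- The effect of 0.8 SD is assumed; the article gives no SDQ effect size.
- Completers: 40 × 0.8 = 32 and 20 × 0.8 = 16.
- Diluted effect: 0.8 × 0.50 = 0.40 at T2; 0.8 × 6/26 = 0.185 at T1.

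| Effect (SD) | 32 vs 16 | 40 vs 20 |
|---|---|---|
| 0.8 (no dilution) | 72% | 82% |
| 0.40 (T2, even averaging) | 25% | 30% |
| 0.185 (T1, even averaging) | 9% | 10% |

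For an effect present from day 1, the range with 32 versus 16 completers runs from 72% (parents in practice rate only the treated weeks) down to 25% at T2 and 9% at T1 (even averaging). Where the truth lies depends on how parents recall, which the article cannot show.

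**After the change.** A 4-week period lies wholly within treatment at T1. At T2 it contains no pre-treatment weeks. The pre-treatment share is then 0% at both visits.

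**The case against.** The SDQ paragraph describes an instrument, and a condensed article may leave the exact form used at each visit to the full protocol or case report form. That is fair: use of the 6-month wording at T1 and T2 is an inference. It is the natural one, since the article states one period and schedules the scale three times, but if a shorter follow-up wording is already in use, the point reduces to saying so.

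The size is also open to challenge. The 0.8 SD effect and the even averaging are assumptions, parents may weight recent weeks more, the SDQ was never powered, and the planned test is a three-group ANOVA rather than a two-sample comparison. All of this stands, so the power figures show scale only. The T2 share is borderline, and on a 24-week count it dips below half. The 6-week analysis is labelled exploratory.

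Three stronger readings are tempting, and the documents support none of them.
- A reader might infer that the SDQ cannot measure the 12-week effect. About 46–50% of the T2 window is on treatment, so the scale measures that effect poorly but not at zero.
- A reader might infer that a null SDQ result would be an artefact of recall. It could equally be genuine.
- A reader might infer that the trial's efficacy finding is biased. All arms share the reference period, so it lowers sensitivity and does not create a false difference. The ABC and CARS comparisons do not depend on it.

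Finally, switching children from a 6-month baseline to a shorter follow-up wording would mix the change of wording with the treatment change in the paired tests. That is a sound objection, and the fix below avoids such a switch.

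**Conclusion.** The point holds as a limited, inexpensive improvement to a secondary outcome. As written, about 77% of the T1 window and 50–54% of the T2 window precede treatment, and the windows overlap baseline by about 77% and 50%. Those shares rest only on the article's dates and a 26-week count.

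The direction of the effect, toward no difference, needs only that parents follow the instruction to some degree. The amount of attenuation, and the fall in power from about 72% to 25% and 9%, needs the further assumptions of even averaging and a 0.8 SD effect from day 1; recency weighting would make the loss smaller and gradual onset would make it larger. A null SDQ result could therefore partly reflect the recall period.

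**What to change.** - For every child not yet assessed at baseline, use one short reference period, for example the past 4 weeks, at T0, T1 and T2, and state it in the SDQ section.
- Keep children who already have a 6-month baseline on that wording throughout, and flag them.
- Run the SDQ analysis with and without the flagged children. The first 8 were allocated 1:1:1 and later children 2:1:1, so wording may be associated with arm.
- If the wording cannot be changed, declare the reduced sensitivity as a limitation and do not interpret the SDQ at T1.

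The change is one line on a questionnaire and touches no treatment, visit or sample size. It has two costs. Early and later children will have different wording; the article reports 8 children randomized, but its timeline shows data collection running from May 2024, so the early group may be larger by the time of the change. The quoted Cronbach α of 0.78 also may not carry over to a shorter period.

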#### RBS-R Measure

This 43-item scale [44] comprises 6 core components: stereotyped behavior, self-injurious behavior, compulsive behavior, ritualistic behavior, fixated behavior, and restricted behavior. Participants’ parents complete the RBS-R, with higher total scores indicating more severe stereotyped behaviors. The Cronbach α coefficient is 0.85. The Chinese version of this scale has shown good reliability and validity, making it an effective tool for evaluating treatment effects on repetitive behaviors in children with ASD.

### Ethical Considerations

This study has been reviewed and approved by the ethics committee of Longgang Maternal and Child Health Hospital of Shenzhen, China (KYXM-2023-032), in accordance with the Declaration of Helsinki. Parents or legal guardians of child patients who meet the inclusion criteria are informed of the study’s purpose, specific procedures, and potential risks and possible benefits of participation. Those who choose to participate then provide written informed consent. Participants’ personal data will be kept confidential throughout the study and accessible only to the research team. There will be no compensation provided to participants, and no identifiable images of individual participants will be included in the manuscript or supplementary materials.

### Statistical Analysis

Statistical analyses will be conducted using SPSS. All participants, including the first 8 randomized under the original scheme, will be analyzed according to the intention-to-treat principle. At baseline, continuous variables among the 3 groups will be compared using the Kruskal-Wallis test, whereas categorical variables will be compared using the chi-square test to assess the balance of demographic and clinical characteristics (including age, gender, and baseline scores on all outcome measures) across the randomized groups.

Data normality will be assessed, and appropriate statistical tests will be selected accordingly. For normally distributed measurement data, between-group comparisons will be conducted using one-way ANOVA, and within-group pretest-posttest treatment comparisons will be made using paired-sample 2-tailed *t* tests presented as means and SDs. For nonnormally distributed data, nonparametric tests will be used, with results reported as medians and IQRs. *P*<.05 will be considered statistically significant.

In addition to the primary end-point comparisons at study completion, an exploratory interim analysis of outcomes at 6 weeks will be performed to preliminarily assess the effects of left DLPFC stimulation.

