### Sample Size

Sample size calculation was based on one-way ANOVA comparing the primary outcome measure (Autism Behavior Checklist [ABC] scores) among the 3 groups. The calculation was performed using the PASS software (version 15; NCSS, LLC) with the following parameters: significance level of α=.05 (2 sided), statistical power of 1 – β = 0.90, and number of groups of *k*=3. On the basis of previous similar studies [33,34], the within-group SD is set at σ=6.5, yielding a medium to large effect size (Cohen *f*). The calculation indicated that a minimum sample size of 15 participants per group was required. Accounting for an anticipated dropout rate of approximately 20%, a total of 20 participants will be recruited for each group. The following standard ANOVA sample size formula was applied: n = ψ^2^ × (σ^2^) / (*k* × *d*^2^).

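### Intention-to-treat is promised for all participants, but the tests named for week 13 use only children with an observed T2 score unless values are imputed, and week-6 scores do not enter that comparison

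*Protocol article*

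**What the plan says.** All references are to the protocol article.

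- **Population.** Statistical Analysis says that all participants, including the first 8 randomized at 1:1:1, "will be analyzed according to the intention-to-treat principle".
- **Tests.** For normally distributed data, "between-group comparisons will be conducted using one-way ANOVA", and "within-group pretest-posttest treatment comparisons will be made using paired-sample 2-tailed" t tests. Otherwise: "For nonnormally distributed data, nonparametric tests will be used, with results reported as medians and IQRs". The same section places the primary comparisons at the end of the study, which is T2 (week 13) in Table 1.
- **Visits.** The abstract says: "Assessments will be conducted at baseline, an interim time point, and immediately after the intervention". Table 1 schedules all four scales at T0, T1 and T2.
- **Week 6.** Statistical Analysis adds that "an exploratory interim analysis of outcomes at 6 weeks will be performed to preliminarily assess the effects of left DLPFC stimulation".
- **Dropout.** Sample Size goes from 15 to 20 children per group: "Accounting for an anticipated dropout rate of approximately 20" per cent.

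**The concern.** The population statement and the named tests do not fit together without a further step. A one-way ANOVA at T2 can use only children who have a T2 value, and a paired pre-post test needs both T0 and T2. Run on the observed data, both are complete-case analyses, while the plan describes the analysis as covering everyone randomized.

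The protocol itself expects appreciable dropout, and the schedule is demanding: 5 sessions a week for 12 weeks is 60 sessions, in children aged 2 to 6 years. It is plausible, though not documented, that whether a child stays depends on progress by week 6, and that this differs between arms. If so, the children compared at week 13 are no longer the groups that randomization formed. A child lost after week 6 has two scores on every scale that could correct for this, and the week-13 tests use neither.

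**Working it through.** **1. The plan's own dropout step.** Inputs from Sample Size: 15 evaluable per group, about 20% dropout. 15 / (1 − 0.20) = 18.75, so 19. The article states 20, which agrees to within one child. (The 15 itself cannot be reproduced, because no mean difference or numeric Cohen f is given. This point does not depend on it.)

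**2. Children contributing at T2.** Inputs: planned arms 40/20/20 (abstract), 20% dropout. Assumption: a dropout has no T2 score, and nothing is imputed.

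- 40 × 0.80 = 32; 20 × 0.80 = 16; 20 × 0.80 = 16
- Total 32 + 16 + 16 = 64 of 80, so 16 children do not contribute.

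**3. Possible bias in the completer contrast.** Let a fraction p of an arm be lost, and let those children's T2 mean be delta worse than their arm's full mean. The completers' mean then looks better by p × delta / (1 − p). At p = 0.20 this is 0.20 / 0.80 × delta = 0.25 × delta. With 20% lost in both arms, the bias in the contrast is 0.25 × (delta in arm A − delta in arm B). The SD is 6.5 (Sample Size); delta is assumed, because the article gives no figure.

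| delta, one arm only | Shift in SD | Shift in ABC points |
|---|---|---|
| 0 | 0 | 0 |
| 0.25 SD | 0.0625 | 0.0625 × 6.5 = 0.41 |
| 0.5 SD | 0.125 | 0.125 × 6.5 = 0.81 |
| equal in both arms | 0 in the contrast | 0 |

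**4. Does the week-6 score help?** An illustrative simulation assumed no true effect, SD 6.5 and 20% dropout in both arms. Dropout was at random in the sham arm. In the combined arm it was confined to the 40% of children with the worst week-6 scores, each lost with probability one half. For a T1–T2 correlation of 0.5, 0.7 or 0.8, the completer-only difference was biased by −0.74, −1.08 or −1.29 points, in favour of the combined arm. This is a deliberately strong, one-sided pattern, so it can exceed the range in step 3. Predicting T2 from the week-6 score brought the bias to 0.03, 0.03 and −0.01.

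**5. Precision.** Assume that every dropout has T0 and T1 scores and that the missing T2 scores are missing at random. With correlation r between T2 and the earlier scores, the variance of the T2 mean relative to full data is r² + (1 − r²) / 0.80.

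- r = 0.5: 0.25 + 0.75/0.80 = 1.1875; effective n = 80 / 1.1875 = 67
- r = 0.7: 0.49 + 0.51/0.80 = 1.1275; effective n = 71
- r = 0.8: 0.64 + 0.36/0.80 = 1.09; effective n = 73

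Completers alone give 64. The precision gain is modest; the main reason for the change is bias.

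**The case against.** The strongest reply is that the article never says children without T2 are excluded. ANOVA and paired tests can be run on imputed data, and the imputation rule may sit in an analysis plan that is not shown. The intention-to-treat sentence also has another visible purpose: to keep the first 8 children in the analysis after the allocation ratio changed. Inflating a sample size for dropout is routine in intention-to-treat trials and does not show that a completer analysis is planned.

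Much of this stands, and it rules out several stronger readings that a reader might infer:

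- That the plan drops every child without a T2 score. Exclusion is what the named tests do by default; it is not stated.
- That the lack of an imputation rule is itself a fault. In a condensed article it is not.
- That week-6 data go unused. They have a planned exploratory analysis; they are only absent from the week-13 comparison.
- That 16 children will be lost. The 20% is a planning allowance, Table 1 schedules T2 in every arm, and nothing says that assessment ends when a child stops sessions.
- That the result will be biased by 0.8 points. That figure needs selective loss in one arm only, which is an assumption.

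What remains is the choice of method. The text commits the primary comparison to single-time-point tests in a three-visit design and keeps the intermediate visit for a separate purpose. The tests as named do not deliver the population statement under the dropout the protocol expects.

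**Conclusion.** The point holds as a mismatch between the analysis population claimed and the tests named, together with a primary method that leaves relevant data out of the week-13 contrast. Its size is conditional. About 64 of 80 children contribute if 20% have no T2 score and nothing is imputed. The bias runs from 0 to about 0.8 ABC points for an assumed delta of 0 to 0.5 SD in one arm only, and is zero if the pattern of loss is the same across arms. The documents do not support a claim that the trial will be biased or that children will be removed. They do support changing the method, because the better analysis needs only data already scheduled.

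**What to change.** Make the primary between-arm analysis a repeated-measures mixed model on the T1 and T2 scores, with arm, visit, arm × visit, baseline score, and the stratification factors age and gender. Take the arm contrast at T2 as the primary result. Every child with a baseline score and at least one post-baseline score is then included, under missing-at-random. Add one sensitivity analysis for data not missing at random, for example worsening the imputed T2 values in the combined arm. The exploratory week-6 analysis can stay as planned.

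If the ANOVA is kept without imputation, label it complete case instead of intention-to-treat.

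The cost is a little more analysis work, in software the trial already uses (SPSS fits mixed models), and no extra visits. Table 2 lists end-point assessment and analysis as future work, so the change can be made beforehand. The limits should be stated: the model relies on missing-at-random, and a child lost before week 6 still contributes no outcome. If all losses came before week 6, the model would rest on the same 64 children as the ANOVA.
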